## Abstract

**Methods/design::**

This is a multicenter, randomized, double-blind, placebo-controlled trial. A total of 140 patients with cerebrovascular disorder and a history of aspiration pneumonia will be recruited from 6 centers and randomly assigned to either the real or sham press needle group in a 1:1 ratio. The press needle will be replaced twice a week. The treatment will be administered bilaterally at acupoints stomach meridian 36 and kidney meridian 3. The primary outcome is the frequency of aspiration pneumonia onset. The secondary outcome is the improvement of the latent time of the swallowing reflex. The study period is of 12-month. The primary outcome will be evaluated throughout the study period, while the secondary outcomes will be assessed at baseline, 1st month, 6th month, and at the end of the investigation period.

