### 2.6. Sample size (14)

The sample size calculation is based on the results of previous studies. The incidence of aspiration pneumonia in previous studies was 0.091 (4/44) in the intervention group and 0.292 (14/48) in the control group.^[17]^ The sample size has been calculated with a 2-tailed significance level of 5% and a power of 80%, resulting in 118 participants (59 in each group). To account for 20 dropouts, the calculation 118 + 20 = 138 suggests that 138 patients should be recruited. This value has been rounded off to 140 patients.

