### 2.7. Recruitment (15)

Potential participants with cerebrovascular disease and a history of aspiration pneumonia will be recruited from the National Hospital Organization Yonezawa Hospital, Minamisanriu Hospital, Kesennuma City Motoyoshi Hospital, Saka General Hospital, Sendai Tomizawa Hospital, and the Ikeno Clinic. The physician will contact the administrator when the patient meets the eligibility criteria. If participants are interested in our study, they will be informed of the purpose and content of the research as well as the benefits and drawbacks of participating in detail. After screening, the participants who meet the inclusion criteria will be enrolled. The study flow is shown in the SPIRIT Figure (Fig. 1). The participants will undergo a 12 months treatment period.

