**Figure 3. F3:**
[figure not shown]
Measurement items and data collection plan. The number of occurrences of aspiration pneumonia and frequency of fever during the 12 months observation period will be determined. LTSR = latent time of swallowing reflex, BI = Barthel index, BMI = body mass index, LTSR = latent time of swallowing reflex, MMSE = mini-mental state examination.

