### 2.11. Statistical methods (20a, 20b, 20c)

#### 2.11.1. Statistical methods for primary and secondary outcomes (20a).

Statisticians will independently undertake statistical analyses. Parametric data will be presented as mean ± standard deviation, whereas non-parametric data as median and 95% confidence interval. Two-tailed *t* tests and chi-squared tests will be used to compare the demographic and clinical characteristics of the 2 groups at baseline. MMSE, BI, and total caloric intake at baseline and endpoint will be compared between the 2 groups using repeated-measures analysis of variance. The number of febrile days in the 2 groups was compared using the 2-tailed *t* test. The probabilities of being pneumonia-free and survival from pneumonia-related deaths will be estimated using the Kaplan–Meier product-limit method. Pneumonia-free survival rates will be calculated from the date of random assignment to the date of pneumonia onset, date of death, or cutoff date for patients alive at the time of closure of the dataset. A Cox proportional hazards regression model will be used to examine the relationship between modifiable factors and the incidence of pneumonia or pneumonia-related mortality. Relative risks) and 95% confidence interval will be calculated from 2-by-2 tables. Plausible predictors (age, sex, ease of diagnosis, duration of illness, activities of daily living, cognitive function, and treatment assignment) will be included in the original model. Backward stepwise regression will be performed, and *P* > .2 will be used for variable removal. Statistical analysis will be performed using SPSS software (version 21.0; IBM, Armonk, NY). All statistical tests will be 2-sided, and the statistical significance threshold will be set at 5%.

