### 2.16. Trial status

The protocol and progress are registered in the University Hospital Medical Information Network (UMIN000023123). Recruitment will begin in January 2022 and is expected to be completed in May 2025.

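### The end date for pneumonia-free survival is tied to closure of the dataset, which contradicts the 12-month observation period and leaves dropouts with no end date of their own

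*Protocol article*

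**What the plan says.** Section 2.11.1 measures pneumonia-free survival from randomisation to pneumonia onset, death, or the "cutoff date for patients alive at the time of closure of the dataset". Those are the only end dates it gives. The same section plans Kaplan-Meier estimates, a Cox model that includes treatment assignment, and relative risks from 2-by-2 tables.

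Other parts of the article fix a 12-month window:

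- Abstract, Methods/design: "The study period is of 12-month. The primary outcome will be evaluated throughout the study period".
- Section 2.7: "The participants will undergo a 12 months treatment period".
- Figure 3 legend: pneumonia occurrences and fever frequency "during the 12 months observation period will be determined".

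Two more statements bear on the point. Section 2.16: "Recruitment will begin in January 2022 and is expected to be completed in May 2025". Section 2.6 adds to the sample size "To account for 20 dropouts".

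**The concern.** A patient with neither pneumonia nor death has one possible end date under section 2.11.1: a cutoff attached to closure of the dataset. Under staggered entry, that date lies well past month 12 for most patients. The same date applies to someone who left observation early, because no withdrawal or last-contact date is offered.

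Two things are at stake in the time-to-event analyses. First, time after month 12 is off treatment and, on the article's description, unobserved. It either adds empty follow-up or, if later pneumonias reach the dataset, mixes an off-treatment comparison into the 12-month question. Second, a dropout kept at risk contributes event-free time that nobody observed. That lowers the estimated risk, and it biases the comparison if the arms lose patients at different rates.

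**Working it through.** **Inputs.** From section 2.6: 12-month risks 0.091 and 0.292, two-sided 5%, 80% power, 59 per group, 20 dropouts. From section 2.16: recruitment January 2022 to May 2025, which is 40 to 41 months depending on the days counted. From the abstract, section 2.7 and Figure 3: 12 months per patient. Assumptions, not in the documents: uniform entry, constant hazards, no competing deaths.

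**1. The plan's own figure.** With pooled variance and mean risk 0.1915:

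n = [1.960·√(2·0.1915·0.8085) + 0.842·√(0.091·0.909 + 0.292·0.708)]² / (0.292 − 0.091)² = (1.091 + 0.453)² / 0.0404 ≈ 59.

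This reproduces 59 per group, 118 in all, and 118 + 20 = 138. It compares two proportions and uses no follow-up time, so the end-date rule does not alter it.

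**2. Length of follow-up under the rule.**

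- Closure 12 months after a last entry in May 2025: 40 + 12 = 52 months, or 41 + 12 = 53, for the first recruit.
- May 2025 read as the end of the trial: about 40 months for the first recruit.
- Entry over 40 months, closure at 52: range 12 to 52, mean 52 − 20 = 32. Share beyond month 12 is 20/32 = 62%.
- Entry over 28 months, closure at 40: range 12 to 40, mean 40 − 14 = 26. Share beyond month 12 is 14/26 = 54%.

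**3. Overrun when no later pneumonias are recorded.** The Cox partial likelihood changes only at event times. With none after month 12, the extra time leaves the estimate as it was, and the Kaplan-Meier curve runs flat to closure.

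**4. Overrun when later pneumonias are recorded and benefit stops at month 12.** Monthly hazards: control −ln(0.708)/12 = 0.0288; treated −ln(0.909)/12 = 0.0080 to month 12, then 0.0288. The 12-month hazard ratio is 0.276. Expected events use 59 per arm. The average log hazard ratio is approximated by (share of events in year 1) × ln 0.276. Power = Φ(√(D/4)·|ln HR| − 1.96), where D is the number of events.

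| Follow-up | Treated events | Control events | D | Share after month 12 | HR | Power |
|---|---|---|---|---|---|---|
| Capped at 12 months | 5.4 | 17.2 | 22.6 | 0% | 0.28 | 0.86 |
| Closure at 40 months | 22.2 | 30.3 | 52.5 | 57% | 0.57 | 0.52 |
| Closure at 52 months | 27.1 | 34.2 | 61.3 | 63% | 0.62 | 0.46 |

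For closure at 52 months, (34.2 − 17.2)/34.2 = 50% of control and (27.1 − 5.4)/27.1 = 80% of treated first events fall after month 12. A log-rank simulation with 60 per arm gave HR 0.31 and power 82% when capped, HR 0.59 and 47% with closure at 40 months, and HR 0.64 and 40–41% with closure at 53 months. If the benefit persisted in full instead, longer follow-up would raise power, to 99% in the same kind of run.

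**5. Dropouts kept at risk to month 12.** If dropout times are uniform over the year, a control dropout has an event seen with probability 1 − 0.292/0.3453 = 0.154, where 0.3453 = −ln(0.708).

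- 10 of 70 drop out: (60·0.292 + 10·0.154)/70 = 27.2%, against a true 29.2%.
- No true effect, 5 against 15 dropouts: (65·0.292 + 5·0.154)/70 = 28.2% and (55·0.292 + 15·0.154)/70 = 26.3%. The relative risk is 0.263/0.282 = 0.93.
- Equal dropout of 20/138 = 14.5% in each arm: risks 0.085 and 0.272, power about 0.83 at 69 per arm. If all leave at the start: 0.078 and 0.250, power about 0.79.

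**The case against.** The best defence is that the article plans pneumonia ascertainment only within 12 months, so no later events would enter and the hazard ratio would not be diluted. The primary outcome in section 2.4 is a number of cases during the study period, and the sample size is for two proportions; neither depends on the time axis in section 2.11.1. The cutoff date is also undefined and could be meant as each patient's month 12. Finally, a condensed article may leave censoring at loss to follow-up to a fuller document.

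Much of this limits the size of the problem:

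- A reader might infer that the trial's planned power is roughly halved. The documents do not support that. The lower figures need recorded events after month 12, which no section plans, benefit that stops at month 12, and a log-rank test that the article does not name.
- A reader might infer that the plan declares dropouts pneumonia-free. It does not say so. That is the literal consequence of offering no other end date. For a dropout whose vital status is unknown, the rule gives no end date at all.
- Under equal dropout the effect is small. The 5 against 15 split is an illustration, not a forecast.

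The contradiction itself stands. The article does not leave the end date open. It states one and ties it to closure of the dataset, which reads as a calendar date. Even on the month-12 reading, withdrawals still have no end date.

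**Conclusion.** The concern holds as an internal contradiction. The stated end date for pneumonia-free survival does not fit the 12-month observation period, and it assigns about 40 to 53 months to an event-free early recruit, depending on when the dataset closes. It affects the Kaplan-Meier estimates and, if it supplies their time axis, the Cox analyses. The overrun does not affect the 12-month count, the 2-by-2 relative risk built on it, or the sample size.

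Its effect on the result is conditional. Without later events, the overrun costs only a misleading plateau. With later events and benefit confined to treatment, the hazard ratio moves from about 0.3 to about 0.6, and log-rank power from about 82–86% to 40–52%, under uniform entry and constant hazards. Separately, dropouts kept at risk lower the risk by about two percentage points at 10 per arm, and bias the comparison if dropout differs by arm.

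**What to change.** In section 2.11.1, replace the end-date rule with: time from randomisation to first aspiration pneumonia or death, with event-free patients censored at the earlier of 12 months after randomisation and the last date known under observation. This keeps death as an end date, as the rule now has it. State that the Kaplan-Meier and Cox analyses both use this time axis. Settle it before the database is locked, so that no cutoff is chosen with results in view.

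The cost is small. The last observation date must be recorded for every patient, and pneumonias after month 12 are left out of this analysis. The sample size stays at 59 per group before dropouts.

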## 1. Introduction (6a, 6b, 7, 8)

In Japan, pneumonia is the fifth most common cause of death worldwide. Moreover, 97% of the deaths due to pneumonia occur among older adults aged ≥65 years. In addition, the ratio of aspiration pneumonia to age-specific pneumonia increases with aging.^[1]^ Among patients with pneumonia aged ≥70 years, approximately 70% are considered to have aspiration pneumonia.^[2]^ Particularly, patients with cerebrovascular disorders are easily affected by aspiration pneumonia.^[3,4]^ In other words, aspiration pneumonitis is an important disease associated with vital prognoses in older adults. Aspiration pneumonia is caused by an influx of saliva and other fluids, particularly at night. A decrease in the swallowing reflex is strongly related to the onset of aspiration pneumonia.^[5]^ Furthermore, physiological changes associated with aging contribute to this decrease.^[6]^ The causes include a decrease in masticatory force due to missing teeth, poor alimentary bolus formation with decreased capacity of saliva secretion, delay in swallowing reflex creation with a decrease in pharyngeal perception, delay of the elevation by the low degree of the laryngeal prominence, and parorexia with a decrease in cognitive function.^[7,8]^ In addition, a history of cerebrovascular disorders results in a decrease in substance P, an important trigger for the swallowing reflex, and reduces swallowing function.^[9]^

Strategies for preventing aspiration pneumonia include improvement of swallowing function with rehabilitation, pharmacotherapy mouth care, prevention of gastroesophageal reflux, maintenance of consciousness, maintenance of nutritional status, and vaccination against pneumococcus.^[10]^ However, the number of patients with aspiration pneumonia has increased.^[1]^ Therefore, novel therapies that improve swallowing function and prevent aspiration pneumonia are required.

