#### 2.2.2. Exclusion criteria.

Patients with serious diseases, such as chronic respiratory diseases, malignancies, and chronic ischemic diseases, that can result in pneumonia.Patients with metal allergies.Patients with severe skin disorders.Patients with no developed swallowing reflex at the time of the initial latent time of swallowing reflex (LTSR) measurement.Patients with 3 or more severe aspiration pneumonia episodes in the past 3 months.

Patients receiving the standard treatment for cerebrovascular disease, its sequelae, and aspiration pneumonia are acceptable. However, the use of high-dose steroids and immunosuppressive therapies are unacceptable.

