### 2.4. Outcomes (12)

The primary outcomes will help determine whether aspiration pneumonia is prevented and if press needle stimulation is effective. The primary outcome is the number of cases of aspiration pneumonia during the study period. Diagnosis of aspiration pneumonia will be made by the attending physician based on the Japanese Respiratory Society Guidelines for the management of hospital-acquired pneumonia in adults. The total number of diagnoses of aspiration pneumonia at the end of the study will be calculated.

Secondary outcomes will help determine whether seal acupuncture improves swallowing function and general conditions. The secondary outcomes are LTSR, fever frequency, Barthel index (BI), body mass index, general blood test results, and mini-mental state examination (MMSE) results. LTSR measures the time between the insertion of an 8 Fr tube through the nasal cavity to the uvula of the palate and the initiation of swallowing after the injection of 1 mL of distilled water. Three measurements are taken and the mean value is calculated. Fever is defined as a body temperature of 37.5°C or more. The number of days with fever during the study period will be determined.

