### 2.9. Data collection (18a, 18b)

An overview of specific measurements and time points for data collection is shown in the SPIRIT Figure (Fig. 3). All data will be collected and recorded on paper-based case report form (CRF) by the investigators. Patient characteristics, questionnaires, and evaluation forms, such as BI and MMSE, findings of LTSR swallowing measurement and number of incidences of aspiration pneumonia, fever frequency, laboratory data, and physical status will be collected. Adverse effects will also be recorded. After recording the data, the investigators will confirm the CRF form by referring to the medical records.

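### The pneumonia Cox model omits baseline swallowing latency (LTSR), which the protocol's own rationale supports and every entrant has measured, and lists an undefined covariate, 'ease of diagnosis'

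*Protocol article*

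**What the plan says.** Section 2.11.1 sets out a Cox model for pneumonia or pneumonia-related death and names its starting terms: "Plausible predictors (age, sex, ease of diagnosis, duration of illness, activities of daily living, cognitive function, and treatment assignment". The list is then reduced: "Backward stepwise regression will be performed, and *P* > .2 will be used for variable removal". Treatment assignment stands on the same list and is not said to be exempt from removal.

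On the swallowing reflex, the Introduction states: "A decrease in the swallowing reflex is strongly related to the onset of aspiration pneumonia". LTSR is the protocol's measure of that reflex (section 2.4). It is measured before entry, because section 2.2.2 excludes "Patients with no developed swallowing reflex at the time of the initial latent time of swallowing reflex (LTSR) measurement". The Abstract adds that "the secondary outcomes will be assessed at baseline, 1st month, 6th month, and at the end of the investigation period".

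On data items, section 2.9 records "Patient characteristics, questionnaires, and evaluation forms, such as BI and MMSE, findings of LTSR swallowing measurement and number of incidences of aspiration pneumonia", followed by fever, laboratory data and physical status. 'Ease of diagnosis' appears only in section 2.11.1.

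**The concern.** The covariates are spelled out, so the absence of LTSR is a stated choice and not a detail left to an analysis plan. A list of plausible predictors leaves out the baseline factor on which the protocol builds its case for the intervention, although the value should be on file for every randomised patient. Section 2.8.1 describes whole random numbers and mentions no stratification, so nothing stated in the design balances LTSR between arms.

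Meanwhile one of the seven places goes to a term that a second statistician could not code from the document. At stake are some power, some protection against a chance imbalance in a prognostic factor, and a model that can be run as written.

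**Working it through.** **1. The plan's own figure.** Section 2.6 gives risks that it says "was 0.091 (4/44) in the intervention group and 0.292 (14/48) in the control group", two-sided 5%, 80% power and 59 per group. With a pooled variance and no continuity correction, the mean risk is (0.091 + 0.292)/2 = 0.1915, and

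n = [1.960 × √(2 × 0.1915 × 0.8085) + 0.842 × √(0.091 × 0.909 + 0.292 × 0.708)]² / (0.201)² ≈ 59.

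The stated 118 is reproduced (power 0.800 at 59 per group). It does not depend on the Cox covariates.

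**2. Expected events and room in the model.**
- 59 per arm: 59 × (0.091 + 0.292) = 22.6 events.
- 70 per arm, if all 140 are followed: 70 × 0.383 = 26.8 events.
- Seven listed terms: 22.6/7 = 3.2 to 26.8/7 = 3.8 events per term.
- LTSR in place of 'ease of diagnosis': still seven terms, so no change.
- LTSR as an eighth term: 22.6/8 = 2.8 to 26.8/8 = 3.4.

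**3. Power with and without LTSR.** Trials were simulated with 59 per arm, exponential event times, and hazards calibrated to 12-month risks of 29.2% and 9.1%. The Cox treatment test was compared with and without a standard normal covariate standing for log LTSR. The hazard ratio per SD of LTSR is an assumption. Runs A and B used 1,000 trials per scenario, run C 1,500.

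| Assumed HR per SD | Run A | Run B | Run C | Gain (points) |
|---|---|---|---|---|
| 1.5 | 0.81 to 0.83 | 0.79 to 0.80 | 0.79 to 0.80 | 1 to 2 |
| 2.0 | 0.79 to 0.84 | 0.80 to 0.83 | 0.81 to 0.84 | 3 to 5 |
| 2.5 | 0.79 to 0.86 | 0.80 to 0.87 | 0.79 to 0.86 | 7 |

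The Monte Carlo standard error of one power figure is about √(0.80 × 0.20/1,000) = 0.013, so the gain at 1.5 is close to noise. These runs leave out the other listed covariates and the backward elimination.

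**4. Chance imbalance.** The between-arm difference in baseline LTSR has standard error √(2/59) = 0.18 SD, and two standard errors are 0.36 SD. An imbalance of that size would shift an unadjusted hazard ratio by about 1.5^0.36 = 1.16 to 2.5^0.36 = 1.39.

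**5. 'Ease of diagnosis'.** The term is absent from the outcomes (2.4), the blinded assessments (2.8.4), the data collection text (2.9) and the caption of Figure 3. However, section 2.9 contains an open category of patient characteristics, and Figure 3 itself cannot be seen. Duration of illness, also on the predictor list, is likewise not named in those places.

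**The case against.** Several points on the other side are sound.

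- **No contradiction and no invalid comparison.** The Introduction gives a causal rationale and commits to no adjustment. Randomisation protects the comparison whether or not LTSR is in the model. This stands.
- **The hazard ratio moving toward 1 is not bias.** Leaving out a prognostic covariate changes the estimand from a conditional to a marginal hazard ratio. With an assumed LTSR hazard ratio of 2.0, the true conditional log hazard ratio was -1.36 against a median marginal estimate of -1.29, that is 0.26 against 0.28. This stands, and the gap is small.
- **The Cox model is not shown to be the primary test.** The primary outcome is a number of cases, the trial is sized on two proportions, and relative risks from 2-by-2 tables are also planned. The power figures therefore describe the Cox treatment test only.
- **The model is already crowded.** With six null covariates plus LTSR, the median treatment log hazard ratio was -1.47 against a true -1.36, an exaggeration. This argues against an eighth term, but not against a substitution.

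A reader might infer that 'ease of diagnosis' is not collected. The documents do not show this, given the open category and the unseen figure, and the same reasoning would wrongly condemn duration of illness. A reader might also infer that it is a post-randomisation variable that biases the treatment effect. That depends on one guessed meaning of an undefined phrase, which could equally be a wording slip for a disease variable. Nor does the protocol rank LTSR above age, daily activities or cognition as a predictor.

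**Conclusion.** The point holds in a limited form. The stated covariate list is a poor choice by the protocol's own reasoning: it leaves out a baseline measure already required of every patient and includes a term that cannot be coded as written. The treatment comparison remains valid.

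The loss is roughly 1 to 7 points of power for the Cox treatment test, together with no adjustment for a chance LTSR imbalance. Both sizes rest on assumed hazard ratios of 1.5 to 2.5 per SD and on the section 2.6 risks. If LTSR is only weakly prognostic, the gain is negligible. For 'ease of diagnosis', what is established is that it is undefined and has no named source, and nothing beyond that. The correction is worth making because it is cheap, not because the analysis would otherwise fail.

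**What to change.** In section 2.11.1:

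1. Put baseline LTSR in the list in place of 'ease of diagnosis'. A log scale is a reasonable default for a latency, though the documents give no distribution.
2. State that LTSR and treatment assignment stay in the model and that the P > .2 backward removal applies only to the other terms.
3. Say what 'ease of diagnosis' was meant to be. If it is a baseline disease variable, name it and its source. If it describes how pneumonia is diagnosed after randomisation, drop it.

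The cost is one or two lines of wording and no new LTSR data. The model stays at seven terms. If a named disease variable is kept alongside LTSR, events per term fall to about 2.8 to 3.4. The change should be made before unblinding, since a covariate added later would look chosen from the data.

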#### 2.2.1. Inclusion criteria.

Patients with cerebrovascular disease and a history of aspiration pneumonia.Patients in the life stage (maintenance or chronic stage) of rehabilitation for cerebrovascular disease.Patients of a joint research facility receiving in patient or home care.

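### The pneumonia model's named predictors leave out recent aspiration-pneumonia history, so the treatment hazard ratio is open to chance imbalance and, if that history is prognostic, to attenuation

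*Protocol article*

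**What the plan says.** All references are to the protocol article.

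- **Outcome (section 2.4).** "The primary outcome is the number of cases of aspiration pneumonia during the study period". Follow-up is 12 months.
- **Entry (section 2.2.1).** "Patients with cerebrovascular disease and a history of aspiration pneumonia" are eligible. Neither the number nor the date of earlier episodes is fixed.
- **Exclusion (section 2.2.2).** "Patients with 3 or more severe aspiration pneumonia episodes in the past 3 months" are excluded, so enrolled patients can have had 0, 1 or 2 such episodes.
- **Randomisation (section 2.8.1).** Allocation is 1:1 from computer-generated random numbers. No stratification factor is named.
- **Model (section 2.11.1).** "A Cox proportional hazards regression model will be used to examine the relationship between modifiable factors and the incidence of pneumonia or pneumonia-related mortality". The starting covariates are listed by name: "Plausible predictors (age, sex, ease of diagnosis, duration of illness, activities of daily living, cognitive function, and treatment assignment) will be included in the original". Then: "Backward stepwise regression will be performed, and *P* > .2 will be used for variable removal".
- **Second summary (section 2.11.1).** Relative risks with a "95% confidence interval will be calculated from 2-by-2 tables", which are unadjusted.

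**The concern.** How often a patient has recently had aspiration pneumonia is a natural candidate predictor of having it again. The exclusion of patients with frequent recent severe episodes suggests that the investigators regard this history as relevant. The entry criteria still admit a wide mix, from a patient with one remote episode to a patient with two severe episodes in the last 3 months.

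The covariate list is stated item by item, so the omission is a choice made in the text and not a detail left to a longer document. As described, neither the design (no stratification) nor the analysis (no covariate) deals with this factor. Two things are at stake:

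- With about 23 expected events, a chance excess of recently ill patients in one arm would move the treatment estimate, and there would be no prespecified adjusted result to set beside it.
- In a Cox model, leaving out a prognostic covariate pulls the treatment hazard ratio towards 1 and so costs some power.

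**Working it through.** **1. The plan's own figure.** Inputs from section 2.6: risks 0.091 and 0.292, two-sided 5%, power 80%. With pooled variance under the null and no continuity correction, mean risk = (0.091 + 0.292)/2 = 0.1915, and

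n per arm = [1.960 × √(2 × 0.1915 × 0.8085) + 0.842 × √(0.091 × 0.909 + 0.292 × 0.708)]² / 0.201²
= (1.0907 + 0.4528)² / 0.0404 = 58.97, so 59.

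Power at 59 per arm is 0.800. The stated sample size reproduces and does not depend on this point. Expected events are 59 × (0.091 + 0.292) = 22.6.

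**2. Chance imbalance.** Let π be the share of patients with at least one severe episode in the 3 months before randomisation. The documents do not give π, so 20% to 60% is an assumption. The standard error of the difference between arms is √(2π(1 − π)/n), and P(|difference| ≥ 10 points) = 2[1 − Φ(0.10/SE)].

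| π | n per arm | SE | P(≥ 10 points) |
|---|---|---|---|
| 0.2 | 59 | 0.074 | 0.17 |
| 0.4 or 0.6 | 59 | 0.090 | 0.27 |
| 0.5 | 59 | 0.092 | 0.28 |
| 0.2 | 70 | 0.068 | 0.14 |
| 0.4 or 0.6 | 70 | 0.083 | 0.23 |

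The normal approximation is slightly low because counts are whole numbers. In the simulation in step 3 (π = 0.4, 59 per arm), 920 to 959 of 6,000 trials had such an excess in the active arm, which is 15% to 16% in one direction.

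**3. Effect of an imbalance on the estimate.** Simulated trials had no treatment effect, 12-month risk 14/48 in both arms, 59 per arm and assumed shares of 60/30/10% with 0, 1 or 2 episodes. Only trials with an excess of 10 points or more in the active arm were kept. The average treatment hazard ratio (exponential of the mean log) was:

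| Assumed HR per episode | Count left out | Count included |
|---|---|---|
| 1.5 | 1.08 | 1.00 |
| 2 | 1.13 | 0.99 |
| 3 | 1.23 | 1.01 |

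**4. Effect on power.** Exponential times were censored at 12 months, with marginal risks held at 4/44 and 14/48, 59 per arm and about 3,000 trials per setting. A Wald test was used, with treatment alone and then with the 0/1/2 count added (shares 60/30/10%).

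| Assumed HR per episode | Power without | Power with | Mean log HR without | Mean log HR with | SE without | SE with |
|---|---|---|---|---|---|---|
| 1 | 0.790 | 0.789 | −1.343 | −1.349 | 0.529 | 0.531 |
| 1.5 | 0.797 | 0.803 | −1.359 | −1.378 | 0.530 | 0.533 |
| 2 | 0.793 | 0.813 | −1.350 | −1.396 | 0.528 | 0.532 |
| 3 | 0.809 | 0.870 | −1.353 | −1.480 | 0.527 | 0.534 |

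Shares of 80/15/5% and 40/35/25% give similar results: at a hazard ratio of 3, 0.797 to 0.862 and 0.797 to 0.855. The standard error does not fall. The gain comes from the estimate moving away from 1: at a hazard ratio of 3 per episode, from exp(−1.353) = 0.26 to exp(−1.480) = 0.23.

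**5. Validity.** With no treatment effect and no conditioning on imbalance, rejection rates were 0.042 to 0.051 without the count and 0.042 to 0.052 with it.

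**The case against.** The case against is substantial.

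- *The count is only a proxy.* A reader might infer that it is the baseline value of the primary outcome. It is not: section 2.2.2 concerns severe episodes over 3 months, while section 2.4 counts all diagnosed cases over 12 months. A count of 0 covers both a mild episode last month and one years ago, and the article does not define severe. This stands, and it limits how prognostic the count can be.
- *It may not be recorded.* A reader might infer that sites must already hold a 0, 1 or 2 for each patient. The exclusion only obliges them to rule out 3 or more. This stands, so the fix needs a form field.
- *Precision.* A reader might apply the linear-model rule that adjustment shrinks the variance by 1 − ρ² and expect a large power gain. Step 4 shows that the rule does not carry over to a Cox model, and the documents give no correlation to put into it.
- *The plan is valid without the term.* This stands. Type I error is unaffected over all randomisations, and any unadjusted factor can be imbalanced by chance.
- *Too many covariates.* Seven predictors on about 23 events is roughly 3 events each (22.6/7 = 3.2), and an eighth makes it 2.8. The ratio is low, but a simulation adding the count to a model that already held five noise covariates showed neither loss of power nor type I inflation. This does not defeat the fix.
- *The primary comparison is not named.* Section 2.11.1 does not say whether the Cox model or the 2-by-2 table carries the treatment comparison. That is a separate point, but both options ignore event history.

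**Conclusion.** The point holds as a worthwhile, low-cost improvement and not as an error that undermines the trial. The named covariates omit a plausible prognostic factor closely related to the outcome, and the randomisation as described does not balance it.

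The size rests on two quantities that the documents do not give: how common recent severe episodes are, and how strongly they predict later pneumonia. Over the assumed ranges, an imbalance of 10 points or more occurs in about 14% to 28% of trials. When it does, it shifts the unadjusted hazard ratio by about 8% to 23% for hazard ratios of 1.5 to 3 per episode. The power gained by adjusting is about 0 to 2 points up to a hazard ratio of 2 per episode and about 6 points at 3.

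Two stronger readings are not supported: that the omission makes the test invalid or biased on average over randomisations, and that the sample size is wrong. If a fuller analysis plan already includes this term and keeps it in the model, the point falls away.

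**What to change.** - Add a field to the screening case report form for the number of severe aspiration pneumonia episodes in the 3 months before randomisation (0, 1 or 2), using the same meaning of severe as the exclusion criterion.
- In section 2.11.1, add this count to the Cox model as one prespecified linear term.
- State that the count and treatment assignment stay in the model regardless of the backward removal rule. Without this, listing the count would not secure the adjustment, and as written the rule could remove treatment too.
- The unadjusted 2-by-2 relative risk can be reported alongside.

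The cost is one form field, a sentence or two of analysis wording, and one degree of freedom against about 23 expected events. No extra patients or visits are needed.
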